#### 2.7.2. Secondary Outcomes

*(1) Office Blood Pressure*. Office BP will be measured using the clinically validated OMRON HBP-1300 medical upper arm sphygmomanometer. Before starting the BP measurement, participants should be relaxed and seated comfortably in a quiet place without speaking for 5 min. An appropriate cuff will be used to measure BP in both arms to detect differences between arms, and the higher value will be used as a reference. Three BP measurements should be recorded at intervals of 1-2 min, and the BP will be recorded as the mean value of the last two readings [29]. For all participants, BP will be measured 1 min and 3 min after standing from a seated position at the first measurement to exclude orthostatic hypotension.

*(2) 24-Hour Ambulatory BP Assessment*. The 24-h ambulatory BP of participants will be collected using a Welch Allyn ambulatory BP monitor 6100 (Skaneateles, NY, USA). During ambulatory BP monitoring, maintaining normal living or working status and avoiding strenuous exercise prevents cuff movement or loosening. If the cuff position moves or is loose, it should be immediately corrected. The measurement interval will be every 30 min during the daytime (6:00 a.m. to 10:00 p.m.) and every 1 h at night (10:00 p.m. to 6:00 a.m.) [30]. The 24-h ambulatory BP monitoring will involve measuring the mean day- and night-time systolic and diastolic 24-h ambulatory BP, coefficient of variation, and average real variability analysis.

*(3) Health-Related Quality of Life*. According to the World Health Organization (WHO), quality of life is defined as an individual's perception of their position in life in the context of the culture and value systems in which they live, and in relation to their goals, expectations, standards, and concerns [31]. This will be assessed according to the Chinese version of the Short Form Health Survey (Short-Form 36). In previous studies, this scale has demonstrated good internal consistency, test-retest reliability, and discriminant validity [32–34]. The scale consists of eight dimensions: physical functioning, role physical, bodily pain, general health, vitality, social functioning, role emotional, and mental health, and two summary components: physical and mental component subscales, ranging from 0 to 100, with higher scores indicating better quality of life [35].

*(4) Composition of Gut Microbiota*. Fecal samples will be collected for subsequent examination, and microbial composition will be analyzed via high-throughput 16S rRNA gene sequencing. We will advise participants not to receive any antibiotics for at least 1 month before sample collection and not consume any food containing probiotics (e.g., yogurt) for 7 days before sample collection.

The 24-h collection kit includes four gel ice packs (Techni Ice), collection bags, and fecal collection instructions and will be provided for fecal sample collection. Research assistants will also give participants detailed oral instructions before they collect fecal samples. In our laboratory, the cool bag will be maintained at 4°C, which has no significant effect on fecal microbiota diversity or composition [31]. Each sample will be stored briefly in a personal collection kit at 4°C and transported to the Guang'anmen Hospital within 24 h. Once at the hospital, the samples will be taken to the laboratory, where they will be aliquoted and stored at −80°C for subsequent analysis of intestinal microbial composition. All microbial community genomic DNA extractions will be performed using the E.Z.N.A.® Soil DNA Kit (Omega Bio-tek, Norcross, GA, USA).

The hypervariable region V3-V4 of the bacterial 16S rRNA gene will be amplified with primer pairs 338F and 806R using an ABI GeneAmp® 9700 PCR thermocycler (ABI, CA, USA) to obtain a polymerase chain reaction (PCR) product. The PCR product will then be purified and quantified, and the library will be constructed. High-throughput sequencing will be performed using the Illumina MiSeq platform (Illumina, San Diego, USA). The raw 16S rRNA gene sequencing reads will be demultiplexed, quality-filtered using Trimmomatic, and merged by FLASH. Operational taxonomic units (OTUs) will be clustered using UPARSE (version 7.1, http://drive5.com/uparse/), and the Quantitative Insights Into Microbial Ecology (QIIME) software will be used to analyze changes in relative bacterial abundance and *α* and *ß* diversity.

### 2.8. Sample Size

We hypothesize that at least a 30% difference in this primary outcome will be detected after the 12-week exercise intervention (defined as a reduction of at least 15% of the drug prescription for each patient) [36]. This 30% absolute difference represents the difference between the assumed 40% proportion of outcome incidence in the Baduanjin exercise group and 10% incidence in the aerobic exercise group. Assuming a two-sided significance level of 5% and a power of 90%, a sample size of 60 patients (30 in each group) will be needed. Considering sample dropout, increasing the sample size by 10%, a total of 68 cases will need to be studied in the two groups. Thus, the sample size was expanded to include 70 cases (35 cases in each group).

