#### 2.3.1. Inclusion Criteria

Male or female, between 65 and 80 years old.Office BP: 120 ≤ systolic pressure (SBP) < 140 mmHg, diastolic pressure <90 mmHg (according to the baseline measured office BP).Stable dose of antihypertensive drugs for at least 3 months.Treated with a moderate dose of two or more antihypertensive drugs for at least 12 months. According to the guidelines, antihypertensive drugs are defined as five major drugs: angiotensin-converting enzyme inhibitors, angiotensin II receptor blockers, beta-blockers, calcium channel blockers, and diuretics (thiazides and thiazide-like diuretics such as chlorthalidone and indapamide).Eligible patients must be willing to participate in the study and provide informed consent.

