#### 2.7.1. Primary Outcome

The primary outcome will be the proportion of participants with antihypertensive medication reduction postintervention; this will be defined as a reduction of at least 15% of total antihypertensives compared with the baseline medical prescription after the 12-week exercise procedure (e.g., patients using 2 or 3 medications need to reduce ≥50% of 1 medication to achieve the primary outcome and patients using 4 or 5 medications need to reduce ≥1 medication). Guidelines recommend that in older patients (>65 years), treated SBP should not be targeted to <120 mmHg; when the SBP is <120 mmHg, the risk of harm appears to increase and outweigh the benefits [4]. Hence, once participants begin to practice Baduanjin or aerobic exercise, they will be required to return for a routine clinical examination every 4 weeks (including office BP measurement and maintenance of antihypertensive drugs); when office BP is <120 mmHg, we will reduce the number of medications taken by the patients.

Once a medication has been reduced, research assistants will closely monitor the participant's response to the reduction (through BP). The research assistants will perform the monitoring according to the procedures outlined in Figure 3, although these will be flexible. The participants will be required to return for at least one routine BP check (every 4 weeks); when the patients' BP is >150 mmHg or when adverse events (AEs) occur, the general practitioners (GPs) will be contacted, and the medication (dose or type) will be readjusted to ensure that the incidence of severe AEs occurring by medication will be very low.

*(1) Self-Monitoring*. Participants will optionally self-monitor their BP at home when they reduce their medication. The protocols developed in the Telemonitoring and Self-Management in Hypertension (TASMIN) trials [26, 27] have been modified and simplified to suit this study. These reduced medications will be monitored using revised protocols. Following training, participants will be advised to conduct self-monitoring at least four times during the BP check week (4 times weekly) after drug withdrawal.

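### The stated 90% power does not hold at the plan's own 40% v 10%, and the 10% control rate is not reconciled with the rule that triggers medication reduction

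*Protocol article*

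**What the plan says.** All references are to the protocol article.

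- **Section 2.8 (Sample Size)** takes an "assumed 40% proportion of outcome incidence in the Baduanjin exercise group" and "10% incidence in the aerobic exercise group". The operating characteristics are given as "Assuming a two-sided significance level of 5% and a power of 90" per cent, from which "a sample size of 60 patients (30 in each group) will be needed". For dropout, "increasing the sample size by 10%, a total of 68 cases will need to be studied", and finally "the sample size was expanded to include 70 cases (35 cases in each group").
- **Section 2.3.1 (Inclusion Criteria)** admits patients with an office SBP of at least 120 and below 140 mmHg, "according to the baseline measured office BP".
- **Section 2.7.1 (Primary Outcome)** has both arms return every 4 weeks, and "when office BP is <120 mmHg, we will reduce the number of medications taken by the patients". Success is a cut of at least 15% in total antihypertensives. Medication is readjusted if BP exceeds 150 mmHg or an adverse event occurs.
- **Section 2.11 (Statistical Analysis)** counts a reduction only if it was made during the intervention and kept to the end of the study. The arms are compared by an unadjusted chi-square or Fisher test.
- **Section 2.6.2 (Control Group)** gives the control arm supervised walking with the same session length, frequency and heart-rate band as Baduanjin.

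**The concern.** There are two separate problems with the same paragraph.

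First, 30 per arm looks too few for 90% power at 40% v 10%.

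Second, the reduction trigger lies at the lower edge of the entry range and is tested repeatedly. A patient whose usual SBP is in the 120s can read below 120 at one visit by ordinary variation. One drug fewer out of two to five is a cut of 1/5 to 1/2 (20%-50%), which meets the 15% definition. If BP then settles back to the 120s or 130s, neither stated ground for readjustment need arise, and the patient counts as a success without any exercise effect. This can happen in both arms. The 10% for the walking arm has to cover these cases plus any real effect of walking, and the plan does not show that it does.

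At stake is how a null result would be read. A trial believed to have 90% power that finds no difference will be taken as evidence that Baduanjin is no better than walking, when the power may have been far lower.

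**Working it through.** **1. The plan's own figure.** Inputs from section 2.8: p1 = 0.40, p0 = 0.10, difference 0.30, mean 0.25, two-sided 5% (z = 1.960), 90% power (z = 1.282).

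n per arm = [1.960·√(2·0.25·0.75) + 1.282·√(0.40·0.60 + 0.10·0.90)]² / 0.30² = 41.7, so 42.

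Other standard formulas give 39 (unpooled variance), 40 (arcsine) and 49 (continuity corrected). None gives 30. At 80% power the same methods give 32 (pooled), 29 (unpooled) and 30 (arcsine), so 30 per arm corresponds to about 80% power. The dropout step does reproduce: 30/0.9 = 33.3, so 34 per arm and 68 in total.

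**2. Power at 40% v 10%.**

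| Method | 30 per arm | 35 per arm |
|---|---|---|
| Normal approximation, pooled | 78% | 84% |
| Chi-square, exact enumeration | 79.6% | 85.2% |
| Fisher, exact enumeration | 71% | 78% |

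The 35-per-arm column assumes that nobody is lost.

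**3. Chance success under the trigger.** From the documents: entry reading 120 to under 140, trigger below 120, reversal above 150. Assumed, because the documents give no figures: usual SBP mean 130-135, between-person SD 6-8, a range of visit-to-visit SDs, a 5 mmHg rise after a reduction and no exercise effect. Visits at weeks 4, 8 and 12 are inferred from the 4-weekly schedule. Reversals for adverse events are not modelled. Each patient's reading is the usual level plus independent visit noise, simulated and conditioned on the entry window.

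| Visit SD (mmHg) | Success by chance, three visits | Two visits only |
|---|---|---|
| 5 | 7%-20% | 5%-16% |
| 6 | 11%-25% | 8%-20% |
| 8 | 18%-34% | 13%-27% |

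The low end of each range is mean 135 with between-person SD 6; the high end is mean 130 with SD 8. At a visit SD of 4, mean 132 and between-person SD 6, the three-visit rate is about 8%.

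**4. Power if the control rate is higher** (exact chi-square).

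| Control rate | 30-point difference kept: 30 / 35 per arm | Baduanjin held at 40%: 30 / 35 per arm |
|---|---|---|
| 10% | 80% / 85% | 80% / 85% |
| 20% | 69% / 77% | 39% / 45% |
| 30% | 66% / 71% | 12% / 14% |
| 40% | 66% / 71% | no difference |

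With the difference kept, the lowest values are at a control rate of 35%: 66% and 70%.

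**The case against.** The strongest reply is that the documents contain no SBP mean, between-person SD or visit-to-visit SD, so every chance rate above rests on outside assumptions. Office BP is the mean of the last two of three rested readings, so a small visit SD cannot be excluded. Some settings do fall below 10%. A reduction first made at week 12 has no period over which it could be maintained, so two visits may be the fairer count. Readjustment for adverse events, and the route through home readings, would remove some successes and are not modelled. The monitoring flow chart is not visible. The assumed effect is also attributed to a cited source.

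All of this stands against one stronger reading: that the trigger rule is proven to produce more than 10% success through BP variation alone. The documents do not support that. With three visits, every setting tried exceeds 10% at a visit SD of 6 or more, but not every setting does at 5 or less.

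A reader might also infer that the trigger is what breaks the 90% power. It is not: the claim already fails at exactly 40% v 10%, before the trigger matters. A raised control rate would lower power further, and would still do so after the arithmetic was corrected. How far depends on whether the 30-point difference survives, since chance successes would raise the Baduanjin rate too.

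None of the reply restores the 90%, and none of it shows how 10% was squared with the entry range and trigger.

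**Conclusion.** The 90% claim is wrong as written. On the plan's own rates and a chi-square test, power is about 80% with the 60 patients said to be sufficient and 85% with all 70. This part rests on no outside assumption.

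The 10% control rate is unreconciled with the plan's own trigger and is likely, but not proven, to be too low. That judgement rests on the SBP mean, SDs, number of visits and post-reduction rise assumed above. If the control rate is in fact 20%-40% and the 30-point difference holds, power is about 66%-69% (30 per arm) or 70%-77% (35 per arm). If Baduanjin stays at 40% and control is 20%, power is 39% or 45%.

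**What to change.** 1. In section 2.8, replace the 90% claim with the correct power for 70 patients: about 85% by chi-square if all are analysed, about 80% if 60 are.
2. Justify the 10% against the entry range, the visit schedule and the trigger, stating the SBP variability assumed and whether a reduction first made at week 12 counts.
3. Show power over control rates of 10%-40%, both with the 30-point difference kept and with Baduanjin held at 40%.
4. In section 2.11, adjust the primary comparison for baseline office SBP, for example by logistic regression with the result also given as a risk difference. Distance from 120 at entry should predict success strongly under this rule. Adjustment recovers some precision but does not remove chance-triggered successes.

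Cost: a rewritten paragraph, one covariate already collected at baseline, and a less favourable stated power. No clinical rule changes and no extra patients are needed. Keeping the 90% claim instead would take 42 per arm at 40% v 10%, or 42/0.9 = 46.7, so 47 per arm and 94 in total after 10% dropout.

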### 2.11. Statistical Analysis

This study will be based on intention to treat (ITT), and the results will be analyzed in accordance with the principle of ITT analysis. Statistical analysis will be performed at two prespecified time points and will be used to determine primary and secondary outcomes. Data from all patients who complete the follow-up will be analyzed according to the group in which they were originally defined. Participants who received reduced medication in the primary outcome analysis will be defined as those who received reduced medication during the exercise intervention and maintained it until the end of the study. The chi-square test or Fisher's exact test will be used to compare the proportion of patients with a primary outcome event between the two study groups. For the secondary outcomes, measurement data will be expressed as mean ± standard deviation (SD), and independence test, normality test, and homogeneity test of variance will be performed for each group. In addition, repeated measurements over time will be analyzed using analysis of variance (ANOVA of repeated measures), and pair comparisons between groups will be performed using the LSD *t*-test (homogeneity of variance) or Tamhane's T2 test (heterogeneity of variance). The composition of the gut microbiota will be analyzed using a nonparametric Mann–Whitney U test for relative bacterial abundance (at baseline and between groups). A Wilcoxon matched-pairs test will be used for comparison to analyze the differences in relative bacterial abundance between the Baduanjin and aerobic intervention groups. A *P*

-value of <0.05 will be taken to indicate a significant difference. All analyses will be performed using the SPSS v.17.0 software package. Every effort will be made to minimize data loss and participant withdrawal or loss during the study period; if the primary outcome or potential confounders' data are missing, a multiple imputation method will be used to fill in missing data.

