The trial will use a rigorous random allocation method, blinded to evaluators and statistical analysts, to reduce bias. Therefore, the test is expected to produce reliable results. However, there are some potential limitations to this test. First, although the sample size has been calculated according to the existing literature and standard formula, the sample size is small and not sufficiently representative. Second, it is challenging to monitor other physical activities of the participants during the study. Although all participants will be required to return to the hospital regularly for supervised intervention, this will not be sufficient to ensure that participants do not exercise outside the intervention period. Finally, due to the nature of the exercise intervention, it is not possible to blind participants, coaches, and investigators in the experiment. However, every effort will be made to ensure that the outcome evaluators and statistical analysts are not aware of allocation of the treatment options.

In conclusion, this trial will evaluate Baduanjin as an adjuvant therapy for medication reduction in older individuals with HTN.

The results of this RCT will help provide evidence to verify the effects of Baduanjin as an adjuvant therapy for reducing the demand for antihypertensives to find the best treatment for controlling HTN.

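### Section 2.8 claims 90% power from 30 patients per group, but its own inputs (40% vs 10%, two-sided 5%) give about 80%, and the planned 35 per group does not reach 90% either

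*Protocol article*

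**What the plan says.** Section 2.8 of the protocol article gives every input of the calculation. The effect is "assumed 40% proportion of outcome incidence in the Baduanjin exercise group and 10% incidence in the aerobic exercise group", an absolute difference of 30 percentage points. The error rates and the resulting size are "two-sided significance level of 5% and a power of 90%, a sample size of 60 patients (30 in each group"). The total is then raised to 68 for 10% dropout and to 70 (35 per group) as the final target. Section 2.4 fixes 1:1 allocation.

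Section 2.11 names two candidate tests, Fisher's exact and chi-square, one of which "will be used to compare the proportion of patients with a primary outcome event between the two study groups". The Discussion (Section 3) says that "the sample size has been calculated according to the existing literature and standard formula". No formula or software is named for the sample size, and no other section gives a different power, a one-sided level or another effect size.

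**The concern.** A two-group comparison of proportions is fully determined once the two rates, the significance level, the power and the allocation ratio are given. All five are stated, so the figure of 30 per group can be checked without outside information, and it looks too small for 90% power.

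At stake is the declared type II error for the primary outcome. A stated power of 90% tells the reader that the trial would miss the assumed effect one time in ten. If the true figure is nearer one in five, a non-significant primary result carries less information than the protocol says. That matters here because the comparator is itself a supervised exercise programme, matched on session length, frequency and target heart rate (Section 2.6).

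**Working it through.** **Inputs** (Section 2.8; allocation from Section 2.4): p1 = 0.40, p2 = 0.10, difference 0.30, mean rate 0.25, two-sided 5% (z = 1.960), 90% power (z = 1.2816), 1:1. For 80% power, z = 0.8416.

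**Step 1. Try to reproduce 30 per group at 90% power.**

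- Unpooled variance: n = (1.960 + 1.2816)² × (0.40×0.60 + 0.10×0.90) / 0.30² = 10.507 × 0.33 / 0.09 = 38.5, so 39.
- Arcsine: h = 2·arcsin√0.40 − 2·arcsin√0.10 = 0.7259; n = 2 × 10.507 / 0.7259² = 39.9, so 40.
- Pooled variance under the null: n = [1.960·√(2×0.25×0.75) + 1.2816·√0.33]² / 0.09 = (1.9365)² / 0.09 = 41.7, so 42.
- Pooled with continuity correction: 48.1, so 49.

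The stated 30 is not reproduced. The smallest two-sided answer is 39.

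**Step 2. Try other readings.** A one-sided 5% level would contradict the text and still gives 32 (unpooled) or 34 (pooled) per group. At two-sided 5% with 80% power the formulas give 28.8 (unpooled, 29), 29.8 (arcsine, 30) and 31.5 (pooled, 32), which bracket the stated 30.

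**Step 3. Power at 30 per group by formula.**

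- Pooled: Φ[(0.30·√30 − 1.960·√0.375) / √0.33] = Φ(0.771) = 78.0%.
- Unpooled: Φ(0.30·√30/√0.33 − 1.960) = Φ(0.900) = 81.6%.
- Arcsine: Φ(0.7259·√15 − 1.960) = Φ(0.852) = 80.3%.

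**Step 4. Exact power.** Every possible 2×2 table is weighted by its binomial probability at 40% and 10%, and the probabilities of tables with p < 0.05 are summed. The last column uses a common convention, assumed here: chi-square unless an expected count is below 5, otherwise Fisher.

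| Evaluable per group | Chi-square, uncorrected | Fisher throughout | Chi-square, Fisher if expected count < 5 |
|---|---|---|---|
| 30 | 79.6% | 70.5% | 79.1% |
| 31 | 81.3% | 72.7% | 80.9% |
| 32 | 82.8% | 74.8% | 82.5% |
| 35 | 85.2% | 78.5% | 85.1% |
| 42 | 91.7% | 87.4% | 91.7% |

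The rows for 31 and 32 stand for 35 per group less 10% (35 × 0.9 = 31.5). Exact chi-square power first passes 90% at about 40 per group; Fisher's test gives 90.6% at 47.

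**Step 5. Check the dropout step.** 60 / 0.9 = 66.7, or 33.3 per group; rounding up to 34 per group gives 68. This step is sound. The error lies in the 60 that it starts from. Starting from 42 per group, 84 / 0.9 = 93.3, so about 94 patients would have to be enrolled against the 70 planned.

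**The case against.** The case on the other side does not dispute the arithmetic; it disputes how far it reaches.

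- **The size of the risk.** A reader might infer that the trial runs a 20% to 30% risk of missing its assumed effect. That range belongs to 30 per group, and its upper end needs Fisher's test in every case. The trial enrols 35 per group, and Section 2.11 can be read as the usual rule of chi-square unless expected counts are small. At the planning rates an expected count falls below 5 in only 3.6% of trials at 30 per group and 0.7% at 35, so power under that rule is almost that of chi-square alone. This objection stands. Section 2.11 also plans multiple imputation for a missing primary outcome, so the number analysed may be closer to 35 than to 31.
- **The choice of test.** A reader might treat the unspecified choice between chi-square and Fisher as a second fault, to be cured by fixing the uncorrected chi-square. The documents do not support this. The rule may sit in an analysis plan that is not shown. Fixing that test would also have a price: its exact type I error at a common 10% rate is 5.4% at 30 per group and 5.7% at 35.
- **The cause.** It is tempting to say that an 80% calculation was labelled 90%. The numbers fit, but no formula is named, so this is an inference only.
- **The admitted limitation.** The Discussion concedes a small sample. That concession concerns representativeness; it does not disclose lower power, and it sits beside the claim that a standard formula was used.

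**Conclusion.** The point holds. The power stated in Section 2.8 does not follow from its own inputs: 30 per group gives about 80% (79.6% by exact chi-square), and 90% needs about 39 to 42 evaluable per group by the formulas without continuity correction. Rounding up to 35 per group does not rescue the claim, even if nobody drops out.

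For the assumed effect, the type II error is about 15% with 35 per group evaluable, 17% to 19% after 10% dropout and 20% to 21% at 30 per group, against the declared 10%. This rests on the protocol's assumed rates of 40% and 10%, 1:1 allocation, a two-sided 5% level and chi-square testing, with or without Fisher's test for small expected counts. If Fisher's test were used throughout, power would be 70.5% at 30 per group, about 73% to 75% at 31 to 32, and 78.5% at 35.

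The conclusion is confined to the stated power. It does not show that 70 patients is an unacceptable size, since chi-square power remains above 80% after the planned dropout.

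**What to change.** Keep 70 patients and restate the power in Section 2.8. Suggested wording: *Thirty evaluable patients per group give about 80% power (chi-square test, two-sided 5%) for 40% versus 10%. With 35 per group enrolled and 10% dropout, power is about 81% to 83%. A power of 90% would need about 40 to 42 evaluable patients per group. Power is lower if Fisher's exact test is used.*

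The remark on the sample size in the Discussion should be brought into line with the corrected figure.

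This is a text change only, with no extra patients and no change to the analysis. The cost is that the published power becomes less favourable. Should the sponsor prefer to keep 90%, the alternative is to enrol about 94 patients (84 / 0.9), which is a much larger change and is not needed to make the document correct.
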